### Study component 3: Consultation template and medical record review

This component will collect anonymised practice-level data to describe the management of OA in primary care via retrospective and prospective medical record review in the eight practices recruited to the study. The OA consultation template will record specific Quality Indicators for the core management of OA which are not routinely recorded in practice. These indicators were established through a systematic review of Quality Indicators of OA [48]. These include pain and functional impairment, provision of information, advice about exercise and weight loss, and advice about pharmacological management such as use of paracetamol and topical non-steroidal anti-inflammatory drugs (NSAIDs).

A download of routine consultation, prescription and other management data related to joint pain and OA will be obtained for the preceding 12 months before the introduction of the template. Data regarding certain co-morbidities, identified as having implications for prescribing behaviours in the management of joint pain and OA, will also be obtained for three years preceding the introduction of the template.

The OA consultation template will then be introduced in all of the eight practices at baseline (six months prior to randomisation of the practices for the cluster RCT described in component 1). Training regarding use of the template as part of routine consultations for patients presenting with a working diagnosis of OA (knee, hip, hand or foot pain) will be provided for the GPs and practice nurses. When a patient aged 45 or over with joint pain consults in any of the eight practices and the GP or practice nurse enters a Read code for OA or one of a selection of joint pain Read codes (see Additional file 4), the OA consultation template will open to allow data entry. The GP or practice nurse undertaking the consultation may complete the template, or bypass the template, as appropriate (for various reasons, such as the joint pain not being related to OA). Data on routine recording of management and Quality Indicators will be collected in the template prospectively at 6 months after baseline and 21 months by downloading anonymised practice data.

### Objectives: Study component 3

To describe the current recording patterns and management of OA in primary care based on a 12-month retrospective download of medical records.To describe change in the recording patterns and management of OA in primary care following (i) activation of the template, and (ii) delivery of the MOAC intervention, based on prospective downloads of medical records.

### Study component 4: Evaluation of the MOAC intervention and the training

This component will evaluate (i) the implementation of the MOAC intervention at the level of the service, HCPs and patients, and (ii) the training. Both qualitative and quantitative methods will be used.

## Evaluation of the intervention

### Practice level evaluation

Observations of a number of relevant meetings will be undertaken. The number of observations will be decided, in negotiation with each intervention practice. The intention is to observe all relevant clinical, management and research meetings to reveal how the intervention is operationalised within practice. In order to document events, observations will be structured and will use audio recordings and an observation framework to capture data for analysis. Secondary data collection will also be undertaken to determine adherence to the intervention. For example, notes of meetings in the practices, MOAC 2 CRFs, patient records, and patient feedback forms will be used to gain an understanding of how the intervention was taken up and delivered.

### HCP level evaluation

In order to capture the complexity of how the intervention is received, delivered and managed by members of the primary healthcare team, a range of methods will be used. These methods include semi-structured face-to-face interviews with HCPs, structured observations of consultations, video-recorded simulated consultations, and secondary data collection (for example, minutes of meetings).

#### GP and practice nurse interviews and focus group

As part of the last training session, all GPs and practice nurses will be invited to participate in a focus group, to ascertain whether, and if so how, their views of OA treatment have changed since the training, and to explore what this means for their clinical practice. GPs and nurses from the intervention practices will also be invited to participate in individual telephone or face-to-face interviews after completion of the intervention. All interviews will be digitally-recorded and fully transcribed and conducted six to nine months following randomisation.

#### Practice nurse observations

Observations of MOAC 2 consultations will be undertaken to gain detailed insight into the consultation itself, the interaction between the nurse and patient, and the actual delivery of MOAC 2 in routine practice. Audio recordings and detailed field notes will capture data for analysis and allow verbal and non-verbal communications to be compared.

#### Video-recorded simulated patient consultations

To evaluate OA consultation behaviour, the GPs in the intervention practices will be invited to undertake video-recorded consultations with simulated patients. The simulated patient will take on the role of one with chronic joint problems, and the GP will be asked to conduct a consultation in which the problems are assessed and a management plan agreed upon. Video-recorded consultations will be undertaken (i) before the training (video 1), (ii) during training (video 2), (iii) one month after training (video 3), and (iv) six months after the training (video 4). Two video-recorded consultations (videos 1 and 2) will be used as part of the training to enable GPs to reflect on their consultation behaviours and video-recorded consultations. Videos 1, 3 and 4 will be used to evaluate change of behaviour after training. Video-recorded consultations will be assessed by four independent and blinded (to the time-point of the video-recording) raters, using a pre-defined rating tool.

### Participant level evaluation

#### Patient interviews

These interviews will be carried out within the four intervention practices. In-depth semi-structured interviews will be undertaken to explore patients’ experiences of the MOAC intervention. The purpose is to understand whether the advice and support offered is relevant to patients, whether they have implemented any of the recommendations, and how this has affected their perception of OA and its management.

For MOAC 1, individual in-depth interviews will be carried out in order to ascertain people’s personal experiences and perspectives of their OA and the consultation. For MOAC 2, dependent on patient preference, either individual or group interviews will be held - bringing together three or four participants per group. The main reason for choosing the group interview is to avoid people feeling that they are being ‘checked up on’ with regards to implementing the advice and support offered in MOAC 2. The discussion within a group setting allows for the focus to be on the relevance and adoption of the intervention rather than on individuals.

The sampling frame for this study will be the MOSAICS consultation questionnaire described previously. In order to explore a range of accounts and behaviours, purposive sampling is required. Further variation will be achieved by selecting patients according to type of pain, age and gender. All interviews will be digitally-recorded and fully transcribed.

Two groups of patients will be purposively sampled:Patients who have attended MOAC 1 will be interviewed soon after they have consulted their GP for their joint problem. An interview guide will provide a flexible framework for questioning, asking, for example; how do you feel the consultation went? Have you done anything differently? What information was given by the GP, and was it relevant/appropriate? How did you feel about being referred to a nurse? Approximately 15 people will be interviewed about their experiences of receiving MOAC 1.Patients who have attended MOAC 2 will, dependent upon patient preference, either be interviewed individually or in small groups after completing up to four consultations with the nurse and returning their three-month consultation questionnaire. An interview guide will also be used and will focus questions around the expectations of the nurse consultation and what happened during the consultation, how the guidebook was used and how they felt about it, and overall what worked and what didn’t. Approximately 15 people will be interviewed about their experience of receiving MOAC 2. These 15 people may not be the same as those interviewed about MOAC 1.

## Evaluation of the training

### Training evaluation questionnaires

Before training, to explore drivers for participation in the study, all GPs and practice nurses in participating practices will be invited to answer two open-ended questions that will focus on (i) their reasons for participating in the study and (ii) the perceived benefits (for clinical practice, for the primary care organisation, for their own role etc.). A baseline questionnaire assessment of knowledge about and beliefs and attitudes to OA and its management in primary care, will also be conducted. We will ask the GPs and practice nurses in the intervention practices who have received training to complete two further questionnaires (one month and six months post-training) to determine any change in knowledge, beliefs and attitudes following the training.

All GPs and practices nurses from the control practices will have the opportunity to attend the training at the end of the study. They will also be asked to complete the same evaluation questionnaire as the intervention practice staff at baseline (pre-training) and one month after the training (post-training).

## Health economics evaluation

The economic evaluation will provide a preliminary analysis of the cost effectiveness (cost-utility) of the template and MOAC intervention compared with template alone, over a 12-month period.

### Objectives: Study component 4

To determine whether the training changes health care professionals' behaviour.To explore change in recording in medical records, and the uptake of core treatments for OA recommended by NICE in all participants consulting with joint pain (hip, knee, hand, foot) and the subgroup coded as OA by the general practitioner, following the MOAC intervention.To explore the cost-effectiveness of the template and MOAC intervention compared with the template alone.To explore patient experiences of their consultation for joint pain and whether the new intervention (MOAC) is acceptable and feasible in primary care (qualitative work).To examine and evaluate the way in which a new consultation for OA can be embedded in routine clinical practice in primary care (implementation).

### Analysis

#### Analysis of the cluster RCT

Baseline characteristics will be compared between treatment arms and presented at the level of: (i) GP-Practice clusters, and (ii) Patient characteristics.

Baseline data for GP-Practice characteristics will include data on the stratification variables for randomisation – *i.e*., practice list size and the number of GP practitioners, median index level of deprivation for the Practice, mean age and gender profile of the Practice populations. Baseline data for patients will include data pertaining to participants’ demographic characteristics, joint problem, management of their joint problem, general health and quality of life.

Balance of baseline characteristics is particularly important to establish for cluster trials given the higher level unit of randomisation and thus the potential for bias in the selection and recruitment uptake of patients. No formal statistical testing will be carried out for differences in baseline characteristics except for the GPAQ communication sub scale [49], as this is measure of the uptake of the model OA consultation by GPs.

Descriptive statistics on mean scores for numerical outcomes and frequency counts and percentages for categorical data will be presented for outcome measures from the consultation questionnaire, stratified by study group (intervention or control). A Linear Mixed Model will be used to analyse primary outcome data (SF-12 PCS). Statistical testing of clinical and process outcomes between study groups will be performed using regression methods (adjusting for age, gender, baseline SF12-PCS and corresponding baseline value, of the outcome being measured, as covariates at the individual-patient level and practice size as a covariate at the practice level). A 3-level mixed-model (linear- or generalised- as appropriate to numerical and categorical outcome data, respectively) will be fitted to test for the effect of the MOAC intervention from baseline across follow-up, taking into account clustering by practice (level 3) and patient (level 2) and repeat follow-up measures (level 1). P-values and 95% Confidence Intervals will be provided with estimates of effect size in the analysis of follow up data. The mixed model assumes that missing data is at least missing at random (MAR). We will examine effect estimates in relation to the indicated clinical marker of 0.3 of an effect size.

### Complier Average Causal Effect Analysis (CACE)

A CACE analysis will be performed to provide an unbiased estimate of treatment effect for patients treated as per protocol specification (treatment administered as per protocol in the intervention arm is based on participants having seen the practice nurse MOAC 2 in the intervention practices).

Key secondary outcomes will be analysed including the Arthritis Self-Efficacy pain subscale [41] and the OMERACT/OARSI responder criteria [42], which combines measures of pain intensity (0 to 10 NRS) and function (subscale of the WOMAC) with global assessment of change to determine if participants are ‘responders’ to treatment.

Sub group analyses will be performed on the primary outcome (SF-12 PCS) as well as Arthritis Self-Efficacy pain sub-scale according to the following:Age group (45 to 64 vs 65 and above);Sex (male vs female);Baseline SF12 – physical component score (cut off at median score);Multi-site pain (less than 2 vs ≥2).

An interaction term (product of the subgroup variable and study group) will be included as an additional term in the regression models to evaluate the subgroup effect.

Sensitivity analyses will be conducted (this will be carried out on primary outcome [SF-12 PCS]), details of which can be found in Additional file 5.

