**Table 1 Tab1:** **MOSAICS study eligibility criteria**

**Eligibility criteria**	
**General practices and health-care professionals**	• Member of the Central England PCRN or a Keele Research Network Practice
	• At least two GPs willing to undertake the study as per protocol, *i.e*., act as a control or intervention practice
	• Willing, and able, to allow one (or for preference two – to allow for cross cover) of their practice nurses to be trained to deliver the MOAC 2 clinics
	• Able to physically accommodate the nurse clinics in the practice
	• Uses the EMIS computerised consultation system
	• Nurses and GPs consenting to follow up by the MOSAICS study team
	• GPs willing to be trained to carry out the MOAC 1 consultations
	• Nurses willing to be trained to carry out the MOAC 2 clinics
	• Nurses who consent to being observed and audio recorded in MOAC 2 clinics
***Patients**	Inclusion Criteria:
	• Males and Females
	• 45 years and over
	• Registered with a MOSAICS study practice
	• Consenting to further contact from the study team and medical record review (consent sought as part of the Patient Population Survey)
	Exclusion Criteria:
	• Excluded via GP screen of practice list
	• Unable to give fully informed consent, *e.g*., learning difficulties or dementia
	• Resident in a care or nursing home
	• History of serious disease, *e.g*., malignancy, terminal illness
	• Unable to consult in the general practice
	• Flagged as excluded from research in that practice

EMIS = Egton Medical Information System; GP = General Practitioners; MOAC = Model Osteoarthritis Consultation; MOSAICS = Management of Osteoarthritis In consultations; OA = Osteoarthritis; PCRN = Primary Care Research Network.

*All patients registered with MOSAICS practices randomised to the intervention arm of the study had access to the MOAC 1 and MOAC 2 clinics, including those who did not consent to be followed up, as these ran as part of normal clinical care within each intervention practice.

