### Study component 1: The cluster RCT

This will be a two-arm prospective pragmatic cluster RCT based in eight general practices in the North West midlands and Cheshire, UK. This trial will test the hypothesis that the MOAC intervention is superior to control and will be a parallel group longitudinal design with repeated measures. Practices will be randomly allocated to two clusters: ‘intervention’ and ‘control’ practices. Stratified block randomisation will be performed with the practices stratified into four largest and four smallest practices by list size. In each stratum, the practices will be randomly allocated by a computerised random number generator using blocking with two practices per study group.

Recruitment to the trial will occur over a six-month period. All practices will use the OA template and will be given standard information on OA for patients and healthcare professionals published by Arthritis Research UK. In four practices, patients will receive the MOAC intervention, while the other four practices will continue to provide usual care. GPs in the intervention arm will be offered training for the initial consultation (MOAC 1), and practice nurses will be offered comprehensive training for follow-up consultations (MOAC 2), to deliver supported self-management of OA. The control practices will have the opportunity to receive the training at the end of data collection.

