### The intervention

#### The MOAC intervention

In order to identify the content of the MOAC intervention, two consensus exercises with GPs, lay participants, practice nurses, community pharmacists, and allied health professionals (occupational therapists, physiotherapists, podiatrists) have been conducted [14,15]. Using the findings of these exercises and theoretical models to guide self-management (WISE) and support patient behaviour change, a three-stage consultation has been proposed. The MOAC intervention comprises of MOAC 1 (initial consultation with GP), MOAC 2 (follow-up visits with practice nurse) [37], and MOAC 3 (dissemination to other HCPs). Consultations will be recorded in the general practices through the use of the joint pain and OA consultation template (Additional file 3 provides the full details of the intervention).

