### The training

Training and educational packages will be developed for GPs and practice nurses by drawing on the work of Michie et al. [29,30]. GPs will receive training on how to deliver the initial consultation (MOAC 1) for a new or established patient consulting with OA and the procedure for referring to a practice nurse for a follow-up OA consultation (MOAC 2). Practice nurses will receive training in how to support and enable patients to self-manage OA, using a patient-centred approach, an OA guidebook, goal setting, pain management and the core NICE recommendations (information and advice, strengthening exercise and aerobic fitness training, and weight management). Nurses will also receive training in how to complete the MOAC 2 case report form (CRF), which will be completed for each patient attending the MOAC 2 consultations. Full details of these training packages will be published separately.

For MOAC 3, members of the wider multidisciplinary team linked to the intervention practices (*e.g*., physiotherapists, occupational therapists, podiatrists, pharmacists) will be invited to workshops to increase awareness of the study and its aims.

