### Patient level evaluation

#### Patient consultation questionnaire

Eligible participants who consented to medical record review and further contact in the initial baseline patient population survey (see component 2), and who subsequently consult with joint pain in one of the four intervention practices will be identified via fortnightly electronic searches of consultation data and receive a consultation questionnaire asking about their consultation experience with the MOAC intervention. This will also be administered to eligible participants in the four control practices, to enable comparison of patient reported clinical outcomes.

The primary clinical outcome measure for the cluster RCT is the SF12 PCS [40]. The primary follow-up time point is six months. Key secondary outcomes include the Arthritis Self-Efficacy pain subscale [41] and the OMERACT/OARSI responder criteria [42]. Other outcome measures collected in the trial can be found in (Table 2). Participants will be followed up at 3, 6 and 12 months after consultation to determine short, medium and long term behaviours and patterns of the uptake of core OA treatments. Process outcome measures will also be collected within the study (*e.g*., achieving Quality Indicators of care).

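### The CACE estimate is called unbiased, but compliance is defined by nurse attendance alone while non-attenders may still receive the GP part of the intervention

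*Protocol article*

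**What the plan says.** The section Complier Average Causal Effect Analysis (CACE) states that "A CACE analysis will be performed to provide an unbiased estimate of treatment effect for patients treated as per protocol specification". No condition is attached. The same sentence fixes who counts as treated: "treatment administered as per protocol in the intervention arm is based on participants having seen the practice nurse MOAC 2 in the intervention practices". Receipt of the GP consultation does not enter that definition.

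Elsewhere the article describes a wider intervention. Under The MOAC intervention: "The MOAC intervention comprises of MOAC 1 (initial consultation with GP), MOAC 2 (follow-up visits with practice nurse", followed by MOAC 3, the dissemination to other health professionals. Under Study component 1: "GPs in the intervention arm will be offered training for the initial consultation (MOAC 1". Under The training, GPs also learn "the procedure for referring to a practice nurse for a follow-up OA consultation (MOAC 2", so MOAC 1 precedes MOAC 2. The footnote to Table 1 says that all patients registered with intervention practices "had access to the MOAC 1 and MOAC 2 clinics". Control practices continue usual care; both arms have the template and the standard information leaflets.

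Entry to the trial does not depend on seeing the nurse. The Patient consultation questionnaire section says that consenting patients "who subsequently consult with joint pain in one of the four intervention practices will be identified via fortnightly electronic searches".

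**The concern.** A CACE analysis that uses allocation as the instrument rests on the exclusion restriction: allocation must not change the outcome of patients who would not comply. Here a non-complier is someone in an intervention practice who never saw the nurse. Such a patient may have consulted a GP trained to deliver MOAC 1, which the protocol itself counts as part of what was randomised.

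Other parts of the article show that MOAC 1 is meant to do something on its own. The Analysis of the cluster RCT section singles out the GPAQ communication subscale for testing between arms because it measures how far GPs took up the model consultation. The patient interviews ask people who have had MOAC 1 whether they have since done anything differently.

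If MOAC 1 helps non-attenders, their benefit is part of the between-arm difference, but the analysis assigns all of it to nurse attenders and divides by the attendance share. The lower the attendance, the larger the distortion. The same analysis section says that effect estimates will be examined against 0.3 of an effect size, so a complier estimate could pass that marker for this reason alone.

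**Working it through.** The CACE section gives no number to reproduce. The check is algebraic, with illustrative values.

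**Inputs**
- Reference effect: 0.3 SD with SD 10 (Sample size section), so 0.3 × 10 = 3 PCS points. It is used here as an assumed true complier effect, c = 3. Note that c is the effect of allocation in patients who attend the nurse, that is, of MOAC 1 and MOAC 2 together against usual care.
- p, the share of intervention-arm participants who see the nurse: not given; assumed 0.3, 0.5 or 0.7.
- d, the effect of allocation in intervention-arm participants who do not see the nurse: not given; assumed 0 to 1.5 points.
- No MOAC 2 in control practices (usual care), so non-compliance is one-sided.
- Estimator: not named in the article. The standard ratio ITT/p is assumed.

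**Formulae**
- ITT = p × c + (1−p) × d
- CACE estimate = ITT/p = c + d(1−p)/p
- Bias = d(1−p)/p, which is zero for p below 1 only if d = 0.

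**Results with c = 3**

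| d | p = 0.3 | p = 0.5 | p = 0.7 |
|---|---|---|---|
| 0 | 0.90/0.3 = 3.0 | 1.50/0.5 = 3.0 | 2.10/0.7 = 3.0 |
| 0.5 | 1.25/0.3 = 4.2 | 1.75/0.5 = 3.5 | 2.25/0.7 = 3.2 |
| 1.0 | 1.60/0.3 = 5.3 | 2.00/0.5 = 4.0 | 2.40/0.7 = 3.4 |
| 1.5 | 1.95/0.3 = 6.5 | 2.25/0.5 = 4.5 | 2.55/0.7 = 3.6 |

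A simulation with 200 patients per arm and SD 10, ignoring clustering, agrees. At d = 1 the mean estimate was 5.31, 3.96 and 3.42 for p = 0.3, 0.5 and 0.7; at d = 0 it was 2.95, 3.00 and 2.97.

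**Position relative to the marker.** With a true complier effect of 2 points, d = 1 and p = 0.5, the estimate is 2 + 1 × 0.5/0.5 = 3.0, which is exactly the 0.3 SD marker.

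**The correction run backwards.** For an assumed d, the complier effect is (ITT − (1−p)d)/p. For example, with ITT = 2.0 and p = 0.5 it is 4.0 at d = 0, 3.5 at d = 0.5, 3.0 at d = 1 and 2.5 at d = 1.5.

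**The case against.** Several arguments on the other side have force.

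- *Not every participant receives MOAC 1.* A reader might infer that all intervention-arm participants come in through a trained-GP consultation. The article does not say so. Entry needs only a joint-pain consultation found by electronic search. GPs are offered training, and a practice needs only two willing GPs. Under Study component 3 the consultation may be with a nurse, and the template may be bypassed when the pain is not thought to be OA. This stands. It makes the average d smaller, but gives no reason for it to be zero.
- *The violation is not shown.* The exclusion restriction concerns effects, not exposure. The article shows that non-attenders can be exposed and that MOAC 1 is intended to act; it does not show that MOAC 1 without the nurse changes six-month PCS. This also stands: the assumption is implausible by design, not demonstrably broken.
- *Baseline adjustment may help.* The baseline questionnaire follows the index consultation and baseline PCS is a covariate, so an immediate MOAC 1 effect may be partly absorbed. An effect that develops later would not be.
- *The size is illustrative.* At p = 0.7 and d = 0.5 the bias is only about 0.2 points, or 0.02 SD. Nothing in the article favours the large-bias corner of the table.
- *Detail belongs elsewhere.* The estimator and its assumptions may be set out in an analysis plan, and Additional file 5, which is not shown, holds the sensitivity analyses. Their absence from the article is therefore no fault. The complier definition and the unconditional claim, however, are both fixed in the article's own text.

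**Conclusion.** The point holds in a limited form. The article claims a property, freedom from bias, that its complier definition does not secure. The ratio estimate is off by d(1−p)/p, where d is the effect of allocation in patients who never see the nurse. With a true complier effect of 3 points it stays at 3.0 if d = 0. At d = 0.5 it rises to between 3.2 and 4.2, and at d = 1 to between 3.4 and 5.3, as p falls from 0.7 to 0.3. The values of p, d and the complier effect, and the use of the ratio estimator, are assumptions.

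The direction follows the sign of d. The estimate is too high if MOAC 1 alone helps and too low if it harms, so it is an upper bound only if d is at least 0.

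A reader might go further and infer that the CACE result is certain to be inflated, or that the trial's main conclusion is at risk. The documents support neither. No effect of MOAC 1 alone is established, and the primary mixed-model comparison of SF-12 PCS by allocated practice does not use the complier definition. The sample size and the 0.3 threshold relate to that between-group comparison. CACE is a supplementary analysis, so the weight is moderate.

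**What to change.** 1. Delete the word unbiased from the CACE section.
2. Keep the MOAC 2 definition, and state beside it that the estimate is valid only if allocation has no effect on the outcome in patients who do not see the nurse, in particular if MOAC 1 alone has none. Add that it is an upper bound only if that effect is at least 0.
3. Report, with the CACE estimate, a sensitivity table of (ITT − (1−p)d)/p for d from 0 to 1.5 points, using the observed p.

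Redefining compliance as receipt of any MOAC component is not preferred. If most intervention-arm participants receive MOAC 1, p approaches 1 and the CACE nearly equals the ITT effect, so it answers no separate question.

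The cost is a change of wording and one table that needs no new data. The downside is a less favourable supplementary estimate wherever d is assumed positive. The primary analysis does not change.

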### Sample size

Published research in musculoskeletal disorders has estimated a minimal clinically important difference (MCID) from 2 to 4 points for the SF-36 version 2 Physical Component Summary (PCS) subscale [39], which has a normalised population standard deviation (SD) of 10. Hence, a difference between groups of 0.3 of an effect size is considered a minimum clinically important difference (MCID) threshold for the purposes of demonstrating superiority in the MOSAICS RCT.

In total, 500 patients will need to be recruited in expectation that 400 will provide data at six months. A total of 400 participants (200 to each arm) will ensure 90% power to detect at least the effect size of 0.3 at the primary time point of six months follow-up given a 5% two-tailed significance level. Randomisation is by practice, so this sample size calculation was inflated to correct for an intracluster correlation coefficient (adjusted ICC of 0.005), varying practice size recruitment was taken into account (including coefficient of variation of 0.5 as per POST trial [ISRCTN40721988]) and inclusive of (×0.67) and × 1.25 respective adjustments for repeated-measures design and 20% dropout allowance.

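### Effect modification by age and baseline PCS is tested on two-level versions of continuous measures, which loses about a third of the information if the effect changes roughly linearly

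*Protocol article*

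**What the plan says.** The subgroup plan stands in the Protocol article, at the end of the section headed Complier Average Causal Effect Analysis (CACE). It has two outcomes: "Sub group analyses will be performed on the primary outcome (SF-12 PCS) as well as Arthritis Self-Efficacy pain sub-scale". Of its four subgroup variables, two are continuous measures cut in two: "Age group (45 to 64 vs 65 and above") and the baseline SF-12 "physical component score (cut off at median score"). The other two are sex and multi-site pain, which this point does not cover.

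The form of the test is also fixed: "An interaction term (product of the subgroup variable and study group) will be included as an additional term in the regression models". The subgroup variable is the one just defined, so the test is study group multiplied by a two-level indicator. No interaction with the continuous values is mentioned.

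The individual values are available. Table 2 records age in years and the SF-12 on a 0-100 scale. The section Analysis of the cluster RCT names both as patient-level covariates: "adjusting for age, gender, baseline SF12-PCS and corresponding baseline value".

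**The concern.** A two-level split treats everyone on one side of the cut as alike and treats two patients just either side of it as different. Where the treatment effect changes gradually with age or physical health, that discards information the trial has already paid for.

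The tests have little power to spare. The Sample size section gives power for the main effect only, and an interaction is estimated much less precisely than a main effect. At stake is the chance of detecting a real modifier, and with it how a non-significant interaction should be read.

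The PCS cut has a second weakness. Its value is set by whoever happens to be recruited, so the boundary between low and high PCS cannot be stated before the data are in.

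**Working it through.** **1. Reproduce the plan's own sample size.** Inputs from the Sample size section: effect size 0.3, 90% power, two-sided 5%, ICC 0.005, coefficient of variation 0.5, repeated-measures factor 0.67, dropout factor 1.25. There are eight practices, so 400/8 = 50 analysed patients per practice.

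- Unadjusted total: 4 x (1.96 + 1.2816)^2 / 0.3^2 = 467 (234 per arm).
- Design effect: 1 + ((1 + 0.5^2) x 50 - 1) x 0.005 = 1.3075.
- With six-month data: 467 x 1.3075 x 0.67 = 409. Recruited: 409 x 1.25 = 511.

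The plan states 400 and 500, so its figures are reproduced to within 3%. Power at 400 comes out at 89.3%.

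**2. Effective sample size for the interaction.** 400 / (1.3075 x 0.67) = 457 independent patients. Two alternatives bracket this figure: 400 / 0.67 = 597 with no clustering penalty, and 400 with neither adjustment.

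**3. Information kept by a split.** For a normal moderator and an effect linear in it, a cut at standardised value c with share p on one side keeps phi(c)^2 / (p(1 - p)) of the interaction information. At the median, c = 0 and p = 0.5, which gives 2/pi = 0.637. The loss is 36%, and 0.637 x 400 = 255.

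**4. Age cut at 65.** The article gives no age distribution for consulters, so this step is an assumption shown as a range. Ages are taken as normal, truncated below at 45. The share kept is the squared correlation between age and the indicator of being 65 or over.

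| Mean, SD parameters | Share 65+ | Information kept |
|---|---|---|
| 62, 10 | 0.399 | 0.657 |
| 65, 10 | 0.511 | 0.652 |
| 65, 11 | 0.518 | 0.656 |
| 67, 10 | 0.588 | 0.634 |
| 68, 9 | 0.634 | 0.615 |

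The loss is about 34-39%.

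**5. Power of the PCS interaction test.** With two equal subgroups, the standard error of the difference in effect is sqrt(16/457) = 0.187 SD. For a difference of 0.3 SD between the halves, as large as the whole target effect, the ratio is 0.3/0.187 = 1.60. Under linearity the continuous test has ratio 1.60 / sqrt(0.637) = 2.01. Two-sided power at 5%:

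| Difference between halves | Median split | Continuous |
|---|---|---|
| 0.15 SD | 13% | 17% |
| 0.3 SD | 36% | 52% |
| 0.6 SD | 89% | 98% |

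For 0.3 SD, across effective sizes 400 to 597, the ranges are 32-45% (split) and 47-63% (continuous).

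**6. Check by simulation.** 3,000 data sets of 456 independent patients, with a normal moderator and a linear effect giving 0.3 SD between the halves: power was 51% with the continuous interaction, 32% with the split, and 33% with the split interaction but the continuous score kept as a main effect.

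**The case against.** The strongest reply is that the plan is conventional and sound in form. Four subgroups are named in advance, on two named outcomes, and each is judged by an interaction term, not by comparing p-values within groups. A stated median rule also prevents a favourable cut from being chosen after the results are seen. The analyses are secondary, the alternative brings an assumption of its own, and at about 52% power the better test would still not be decisive. All of this stands, and it limits the point to a modest improvement.

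A reader might also infer more than the article supports:

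- **That both variables are cut into halves, with the 64% figure applying to both.** Only PCS is cut at its median. Age is cut at a fixed 65 years with unknown shares, so its loss rests on assumed distributions.
- **That the split always costs power.** The article gives neither the distribution of either variable nor an expected form of effect modification. With a true threshold at the cut, the split loses little or nothing, and a linear term could do worse.
- **That the PCS subgroup cannot be reproduced elsewhere.** Once the median is reported, anyone can apply it. What holds is that the cut is sample-dependent and unknown beforehand. The age cut has neither problem.
- **That PCS should instead be taken from the population survey.** Which questionnaire supplies baseline PCS is a separate question from whether the score is split, and nothing shown here argues for a change.

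**Conclusion.** The point holds as a minor inefficiency in the stated method. It is not a detail left to a document that is not shown: the article itself fixes both the cuts and the product term, and it cites Additional file 5 only for sensitivity analyses of the primary outcome.

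For PCS, the split gives up 36% of the interaction information if the score is roughly normal and the effect changes about linearly with it. For age, the loss is about 34-39% under the assumed distributions. The power figures also take over the plan's ICC, cluster-size variation and repeated-measures factor, and range as shown when those adjustments are left out. The main-effect analysis, its sample size and the primary conclusion are untouched.

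**What to change.** Make the pre-specified interaction tests study group by age in years and study group by baseline PCS score, each as a linear term, in the models for SF-12 PCS and Arthritis Self-Efficacy pain. Keep 45-64 against 65 and over, and the two median-split PCS groups, only to display estimates with confidence intervals, and report the median value used.

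The cost is one model term for each moderator. No new data are needed and no planned table is lost. The downside is the linearity assumption, which should be stated with the results.
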